## Abstract

**Background:**

Polypharmacy and the use of potentially inappropriate medications are common among nursing home residents and are associated with negative outcomes. Although deprescribing has been proposed as a way to curtail these problems, the best way to implement multidisciplinary comprehensive medication review and deprescribing and its real impact in specific high-risk populations, such as nursing home residents, is still unclear. This multicenter randomized controlled clinical trial aims to assess the effects of a multidisciplinary mediation management program on medication use and health problems.

**Methods:**

A total of 1,672 residents aged ≥ 65 years from 22 nursing homes in South Korea who meet the targeted criteria, such as the use of ≥ 10 medications, are eligible to participate. The experimental group will receive a comprehensive medication review, deprescription, and multidisciplinary case conference with the help of platform. Outcomes will be measured at baseline, at the end of the intervention, as well as at 3, 6, 9, and 12 months after the end of the intervention. The primary endpoints will be the rate of adverse drug events, number of potentially inappropriate medications/potentially inappropriate medication users/two or more central nervous system drug/ central nervous system drug users, delirium, emergency department visits, hospitalization, and falls. The secondary endpoint will be the number of medications taken and polypharmacy users.

**Discussion:**

Our trial design is unique in that it aims to introduce a structured operationalized clinical program focused on reducing polypharmacy and potentially inappropriate medications in a nursing home setting with large samples.

**Trial registration:**

Ethical approval was granted by the public institutional review board of the Ministry of Health and Welfare (2022-1092-009). The study is also registered with the Clinical Research Information Service (Identifier: KCT0008157, Development and evaluation of a multidisciplinary medication management program in long-term care facility residents Status: Approved First Submitted Date: 2023/01/18 Registered Date: 2023/02/03 Last Updated Date: 2023/01/18 (nih.go.kr) https://cris.nih.go.kr/), which includes all items from the World Health Organization Trial Registration Dataset.

**Supplementary Information:**

The online version contains supplementary material available at 10.1186/s12877-024-04844-2.

## Background

A high prevalence of polypharmacy, defined as the concurrent use of five or more drugs, is observed among older adults [1]. Although sometimes necessary to treat multiple conditions, polypharmacy has many drawbacks, the most important being an increased risk of drug-related problems, and is a heavy burden for both the patient and the healthcare system [2]. In addition, polypharmacy increases the probability of the use of potentially inappropriate medications (PIMs) [2]. Older adults living in long-term care facilities (LTCFs) are at risk of polypharmacy and PIM use. One study reported that 70% of LTCF residents received five or more prescribed medications [3], and another study reported that approximately 40% of LTCF residents received PIMs compared to 20–25% of older adults living in the community [4]. In South Korea, the average number of medications taken by residents in an LTCF was reportedly 10.6 ± 4.2, those taking ≥ 11 constituted 45.7% [5], and PIM users were reported at 40.7% [6].

Recently, deprescribing, the process of tapering or stopping drugs supervised by a multidisciplinary healthcare professional aimed at minimizing polypharmacy and improving patient outcomes, has emerged as a useful way to reduce both polypharmacy and PIM use [7, 8]. However, research conducted in LTCF residents is still scarce. Furthermore, no systematic approaches to practice are routinely embedded in clinical care to reduce polypharmacy and PIM use among LTCF residents [9].

In this study, we propose testing a multidisciplinary medication management program (MMMP) for LTCF residents, an intervention designed to be suitable for routine use in LTCF settings. We hypothesized that deprescribing via the MMMP would decrease drug-related problems, including the number of medications and PIMs, and improve health-related outcomes.

## Methods/design

### Aim

We will assess the effects of implementing the MMMP in addressing polypharmacy and PIM use and on a range of health-related outcomes and healthcare service use in adults aged ≥ 65 years who meet the targeted criteria in an LTCF setting. The study will be conducted using a cluster randomized controlled trial (RCT) design with participants belonging to the same group (intervention or control group) within the LTCF.

### Multidisciplinary medication management program in long-term care facility residents

The MMMP in LTCF residents is a structured operationalized clinical pathway for comprehensive medication review (CMR), deprescribing, and multidisciplinary case conferences (MCC) by a team that includes visiting physicians, pharmacists, and nurses in partnership with the participants. In South Korea’s LTCF, a physician is not a resident, but they work outside and regularly visit the LTCF to administer treatment. Therefore, LTCF residents receive treatment from these physicians (visiting physicians) or from external physicians who treated them before they entered the LTCF. The MMMP uses an underlying secure digital platform (pacen-mmmpin.com (PACEN (website.ne.kr)], which integrates evidence to support multiple tools to check whether it is PIMs or not and cumulative medication burdens. This platform integrates consultation elements and evidence support across providers in shared electronic records.

### Design

This is a prospective, cluster randomized, controlled, and open-label study comparing two LTCF residents’ group care strategies: (1) the intervention group, receiving an MMMP including CMR, deprescribing, and MCC, and (2) the control group, receiving typical usual care. The open procedure is the only possible option because of the nature of the intervention, which requires healthcare workers and participants to not be blinded. The study protocol was designed according to the Consolidated Standard of Reporting Trials (CONSORT) Statement. The Standard Protocol Items: Recommendations for Interventional Trials (SPIRIT) checklist and figure (Fig. 1) were used to prepare the study protocol. A flowchart showing an overview of the study is presented in Fig. 2.

**Fig. 1 Fig1:**
[figure not shown]
Standard Protocol Items: Recommendations for Interventional Trials (SPIRIT) figure with study timeline and data collection time points. T1 baseline, T2 3 months (end of the intervention), T3 6 months (3 months after the end of the intervention), T4 9 months (6 months after the end of the intervention), T5 12 months (9 months after the end of the intervention), T6 15 months (12 months after the end of the intervention). ADE, adverse drug event; CNS, central nervous system; LTCF, long-term care facility; PIM, potentially inappropriate medication

**Fig. 2 Fig2:**
[figure not shown]
Flow chart with an overview of the study steps. LTCF, long-term care facility; MT, multidisciplinary team; PHA, pharmacist; PHY, physician

### Recruitment of participants and long-term care facilities

Recruitment for the trial began in April 2022 and is expected to continue until late 2023. The investigators will recruit the LTCFs through direct contact. The nursing home (NH) associations in Seoul, Gyeonggi-do, and Incheon will support recruitment through direct mail to their members, as will the professional association of LTCF physicians. The lead implementation provides methodological support and is responsible for the overall coordination of the study and implementation of interventions.

Participants will be identified through electronic medical records (EMR), history taking, and inter-professional discussions with nurses and research assistants at the LTCFs. Nurses in the LTCF will obtain consent from residents and guardians. If the resident is a patient with dementia and cognitive problems or is unable to sign the consent form, the same will be obtained from the legal representative (spouse, lineal ascendants, or descendants). Recruitment will continue until 76 residents of the LTCF have been included or until 76 residents in one cluster participate.

### Education for pharmacists and nurses in the long-term care facilities

The pharmacist will perform the CMR for the participants, who will be educated on the methodology of performing CMR before the study by attending a course organized by researchers at the college of pharmacy. A separate education session will be organized in each LTCF for nurses and workers, presenting the conduct and documents of the study and introducing them to the platform.

### Participants

To reach the target sample, when a participant is admitted, the nurses and research assistants performing the clinical examination review the inclusion criteria and consider the participant’s eligibility for the study. South Korean is composed of relatively homogeneous ethnic groups.

#### Inclusion and exclusion criteria

The source population will include residents of LTCF. All residents rostered are eligible for participation, provided they fit the inclusion and exclusion criteria.

Participants meeting the following criteria will be eligible for the trial:Aged ≥ 65 yearsA resident who meets one or more of the following criteria` New residents admitted to the LTCF within 4–6 weeks` Residents discharged within 1 month before the researcher’s visit date` Those having experienced a fall or fracture within 3 months before the researcher’s visit date.` Those requiring a long-term care level of 1 (those who were completely dependent on others’ help in daily life)` Those taking ≥ 10 medications, excluding essential medications` Those taking medications that may be misused (e.g., narcotic painkillers and inhalers)` Those taking medications with a narrow margin of safety or high-risk drugs (e.g., narcotic analgesics, antiepileptic drugs, digoxin, theophylline, immunosuppressants, anticancer drugs, anticoagulants, insulin, and benzodiazepines)` Those with suspected adverse drug events (ADEs) before or during admission to an LTCF` Those requesting care from visiting physicians, nurses, pharmacists, and caregivers

Participants will be excluded based on the following exclusion criteria:` Those quarantined for infectious diseases` Those receiving regular medication prescriptions at a tertiary general hospital (this is because according to the research team’s analysis, the risk of PIMs is relatively low when the long-term prescription is for more than 90 days)` Those with a predicted life expectancy of less than 6 months by a visiting physiciansor nurse (e.g., terminal cancer)

### Allocation and randomization

LTCF clusters will be randomly allocated in a 1:1 ratio to either the intervention or control group. A randomization sequence will be generated using a computerized system. All participants in one LTCF cluster will be assigned to the same group.

#### Randomization

Computer-generated randomized lists will be drawn before beginning the study. The LTCF clusters will be randomized to either the control group or the intervention group in a 1:1 allocation ratio. An open-label study is the only option because of the involvement of the participants in the medication reconciliation procedure.

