#### Blinding

Participants will not be blinded to the allocation because this is not practically or economically feasible. Moreover, given the nature of the intervention, no blinding is possible at the LTCF level or for the researchers, and only the statistician performing the analysis will be blinded; unblinding will occur only after the completion of the analysis.

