In our study, participants and researchers are not blinded due to the nature of the intervention (open-label study). To minimize the bias caused by this, we implemented cluster study design. Additionally, in order to minimize performance and detection bias, the study will be conducted according to a pre-determined method according to the protocol. Moreover, if there are indicators with significant differences between the intervention group and the control group when analyzing the results later, they will be adjusted using statistical techniques. Furthermore, in order to minimize attrition bias in the outcome analysis, we will follow the intention-to-treat approach, and data on those who dropped out will be obtained and analyzed from data of the National Health Insurance Sharing Service (It refers to a vast amount of data amounting to 1.3 trillion cases, including demographic information about each patient, details of prescribed drugs, prescribed medical tests and health checkup results, and long-term care insurance data for the elderly, of all citizens).

We developed a multidisciplinary medication management program (comprehensive medication reviews, deprescribing, and multidisciplinary case conferences) to assess its impact on medication use and health problems among LTCF residents. This program, with a high level of evidence as a study with a long-term follow-up period targeting a large population, is immediately scalable, and the results of the trial, if successful, are anticipated to be directly translatable into clinical practice [9] and will become a part of routine preventive care in LTCF residents. Evidence from this study will help to understand the provision of a systematic approach to reducing the burden of polypharmacy and PIMs, as well as providing a systematic clinical pathway for implementation. Based on our results, intervention methods suitable for other settings should be developed.

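### No concealment of a home's arm is stated before its residents are enrolled by unblinded staff, and the cluster design is wrongly credited with minimising open-label bias

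*Protocol article*

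**What the plan says.** - **Unit and timing of allocation.** Under Allocation and randomization, "LTCF clusters will be randomly allocated in a 1:1 ratio to either the intervention or control group", and "All participants in one LTCF cluster will be assigned to the same group". Under Randomization, "Computer-generated randomized lists will be drawn before beginning the study".
- **Screening.** Under Participants, "when a participant is admitted, the nurses and research assistants performing the clinical examination review the inclusion criteria". The recruitment section adds that residents are identified from the electronic medical record (EMR), history taking and discussion between nurses and research assistants.
- **Consent and cap.** The recruitment section says "Nurses in the LTCF will obtain consent from residents and guardians", and "Recruitment will continue until 76 residents of the LTCF have been included". It gives no order in which eligible residents are approached.
- **Eligibility.** One targeted criterion is enough. Most are objective (drug count, listed drugs, care level 1, recent fall). Two leave room for judgement: a suspected adverse drug event and a request for care. The life-expectancy exclusion is judged by a visiting physician or nurse.
- **Blinding.** "no blinding is possible at the LTCF level or for the researchers"; only the analysing statistician is blinded.
- **Claimed protection.** After noting that the study is open-label, the Discussion says: "To minimize the bias caused by this, we implemented cluster study design". It also relies on conduct according to protocol, adjustment for indicators that turn out to differ significantly, and intention-to-treat analysis with insurance data for dropouts.

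**The concern.** In a cluster trial, randomisation balances the homes. It balances the residents only if they are identified and enrolled without reference to the arm. Here the people who screen and take consent belong to groups that the protocol declares unblinded, enrolment is rolling, and part of the eligibility decision is theirs. A nurse trained in the programme may notice suspected drug events more readily or put forward residents thought likely to benefit. A guardian may answer differently when the home's arm is known. The arms could then differ at baseline in measured and unmeasured ways that analysis cannot fully remove.

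The Discussion sentence adds to the problem because it presents the cluster design as the answer to open-label bias. Allocating whole homes keeps the programme from spilling over to control residents in the same home. It blinds nobody, and it is what makes enrolment after allocation possible.

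**Working it through.** **1. Sequence, from the text.** The list precedes the study. Residents are screened as they are admitted, so enrolment in a home is spread over time. Screeners and consent-takers are facility nurses and research assistants, and the blinding section covers both sites and researchers. No sentence keeps the arm hidden from a home until its enrolment closes. Once the programme is running in a home, later admissions can hardly be enrolled in ignorance of the arm.

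**2. Do the stated safeguards reach this?** Adjustment is triggered by a significance test and covers only measured indicators. Intention-to-treat and insurance data deal with dropouts, not with who was enrolled. Cluster allocation deals with contamination. None controls entry.

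**3. The plan's own figures.** 22 homes × 76 = 1,672, as stated. 1,430 / 22 = 65 evaluable residents per home, so 11 × 65 = 715 per arm, as stated. The control PIM-user rate is 40.7%. With the stated odds ratio of 0.41, the intervention odds are 0.41 × 0.407/0.593 = 0.281, a rate of 22.0%. At two-sided 5% and 95% power, the unclustered size is 157 per arm (167 with continuity correction). No intracluster correlation (ICC) is given. Back-calculating from 715: the design effect is 715/157 = 4.55, so ICC = 3.55/64 = 0.056; with 167 it is 0.051. An assumed range of 0.05–0.057 therefore fits the stated size.

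**4. Illustration (assumed shifts, not estimates).** Assume no treatment effect, 11 homes of 65 per arm, and a simple comparison of arms with no baseline adjustment. Selection alone moves one arm's PIM-user rate from p1 = 0.407 to p2.

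- OR = [p2/(1−p2)] / [p1/(1−p1)]
- SE = √{[ICC + (1−ICC)/65] × [p1(1−p1) + p2(1−p2)] / 11}
- Rejection probability: noncentral t, 20 df, noncentrality |p1−p2|/SE, critical value 2.086

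For a 5-point fall, p2 = 0.357 and OR = 0.555/0.686 = 0.81. At ICC 0.05 the bracket is 0.05 + 0.95/65 = 0.0646, so SE = √[0.0646 × (0.2414 + 0.2296)/11] = 0.0526. The noncentrality is 0.05/0.0526 = 0.95, which gives 14.8%.

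| Shift | Spurious OR | ICC 0.02 | ICC 0.05 | ICC 0.057 |
|---|---|---|---|---|
| −3 points | 0.88 | 11% | 8% | 8% |
| −5 points | 0.81 | 23% | 15% | 14% |
| −10 points | 0.65 | 71% | 45% | 42% |

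The nominal rate is 5%. A normal approximation in place of the t gives 16% and 49% for the 5- and 10-point shifts at ICC 0.05.

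**5. Direction.** The same formulas with a 5-point rise give OR (0.457/0.543)/0.686 = 1.23 and about 13–14% rejection at ICC 0.05–0.057, now against the programme. Choosing residents with suspected drug events could well raise PIM use in the intervention arm, so the sign cannot be presumed.

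**The case against.** The strongest reply is that the article dates the list, not its disclosure. Drawing a list early is normal and harmless if it is concealed, and no sentence says when a home learns its arm. The interventions section even speaks of each included participant being randomised, which taken literally puts inclusion first. The article is a condensed account, its flow charts are not reproduced in the text at hand, and the supplement describing the operational steps is not shown. This stands in part: a reader might infer that homes certainly know their arm when they recruit, and the document does not establish that.

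A reader might also infer it from consent and registration being Steps 1 and 2 under the intervention group. That proves little, because control residents must consent too.

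It is fair to add that identification uses the EMR and research assistants as well as nurses, that most criteria are objective, and that PIM use is measured at baseline. These narrow the scope for selection but do not close it. Research assistants are not exempted from the unblinded researchers, one discretionary criterion is enough to qualify, and adjustment depends on a significance test.

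What survives is the combination the article does state: unblinded recruiters, rolling enrolment, some discretionary criteria, and a protection attributed to the wrong feature of the design.

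**Conclusion.** The concern holds in limited form. As written, the plan allows enrolment to depend on the arm, makes this likely through rolling recruitment in unblinded homes, and states no concealment that would prevent it. The Discussion sentence on the cluster design is wrong whatever the concealment arrangements were.

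The size and direction of the bias are unknown. The 14–15% false-positive rate for a 5-point shift rests on an assumed shift, an assumed ICC of 0.05–0.057, 11 homes of 65 per arm and no baseline adjustment. A reader might take it as the trial's actual type I error, or conclude that the bias favours the programme. The document supports neither. The design point does not depend on these figures.

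**What to change.** **Homes not yet opened.** List eligible residents from the EMR, approach them in random order up to 76, and complete consent and T1 before the home is told its arm. Residents may still be added after disclosure so that the target of 76 is not put at risk, but flag them and exclude them in a sensitivity analysis.

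**All homes, including those already recruiting.** Report the numbers eligible, approached and consented by arm. Adjust for the T1 value of the outcome by prespecification, not after a significance test. Run a sensitivity analysis restricted to residents who qualify on objective criteria (drug count, listed drugs, care level 1, recent fall).

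**Text.** State when each home learns its arm. Reword the Discussion sentence so that the cluster design is credited only with limiting contamination. If concealment until enrolment was in fact practised, say so.

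**Cost.** The programme starts later in homes not yet opened, screening records must be kept, and there is some extra analysis. Recruitment began in April 2022, so reordering cannot help homes already enrolled. For those, the counts and sensitivity analyses can expose bias but not fully remove it.

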### Experimental and control interventions

Each participant included in the study will be randomized into one of the following two groups:

Control group

The control group will receive the typical clinical care, as routinely provided in the LTCFs where the study will take place. The only restriction applied would be that no other planned CMR, deprescribing, or MCC will be performed in the LTCF setting during this phase.

Intervention group

We developed an MMMP for LTCF residents as a multifaceted intervention that integrates available evidence tools and a team approach within a clinical pathway where decision-making is led by considering participants’ priorities.

The research team including physicians, pharmacists, and nurses will be informed of the approach and program development so the intervention is as “fit for purpose” and as feasible as possible [9]. To foster fidelity, participating visiting physicians, pharmacists, and nurses in LTCF will receive an in-person training session for the program and the entire intervention, as well as a demonstrative manual [9].

This program will be operationalized as a structured clinical pathway in an electronic web-based platform, called “MMMP in LTCF” (pacen-mmmpin.com [PACEN; website.ne.kr]). It serves as a shared record for all visiting physicians, pharmacists, and other relevant workforces participating in the pathway for access and review. It is designed to be used in conjunction with and complement the EMR. This platform records and integrates five domains (Supplementary Text 1).

Operational steps (Fig. 3)STEP 1: Explanation of the study and obtaining informed consentSTEP 2: Recruitment and registration of participantsSTEP 3: Collection of participant’s informationSTEP 4: Listing medications taken by the participantSTEP 5: CMR and counseling by pharmacistsSTEP 6: Visiting physicians’ referral for medication reconciliationSTEP 7: Medication reconciliation after the prescribing physician confirms the CMR results.STEP 8: Conducting MCC through the cooperation of multidisciplinary teams (visiting physicians, pharmacists, nurses, and NH workers)STEP 9: Sharing CMR results, deprescribing, and participant managementSTEP 10: Nursing care and monitoring of ADEs by nursesSTEP 11: Medication management education for the multidisciplinary teams in the LTCF.

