### Loss to follow-up

We anticipated a conservative maximum loss to follow-up rate of 15%. Participants lost to follow-up will be classified as such because they elected to no longer be part of any further follow-up (withdrawal of consent) or were unable to participate because of discharge, hospitalization, death, etc. In the case of discontinuation of research at an LTCF before the completion of the registration of 76 participants, the target of one cluster, participants already registered at the LTCF are included in the study for intervention and follow-up, and the remaining participants are recruited from other similarly-sized LTCFs (number of residents). In cases where participants who are lost to follow-up do not explicitly withdraw consent, medication and healthcare utilization data will still be collected from participant charts via chart audits where possible [9].

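### The article states no balancing of the 22 homes on known characteristics, and its only stated remedy for imbalance is adjustment triggered by significant differences at analysis

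*Protocol article*

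**What the plan says.** Two sections of the protocol article describe the allocation. Under Allocation and randomization, "A randomization sequence will be generated using a computerized system"; under Randomization, lists are drawn before the study starts and "The LTCF clusters will be randomized to either the control group or the intervention group in a 1:1 allocation ratio". Both make the home the unit. Neither mentions strata, matching, minimisation or a covariate constraint.

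Two home characteristics known before allocation appear elsewhere. In the section on recruitment, "The nursing home (NH) associations in Seoul, Gyeonggi-do, and Incheon will support recruitment", so region is known. Under Loss to follow-up, if a home stops before enrolling its 76 residents, "the remaining participants are recruited from other similarly-sized LTCFs (number of residents"), so size is known and is used to choose a replacement.

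The Discussion states how differences between arms will be handled: "if there are indicators with significant differences between the intervention group and the control group when analyzing the results later", those indicators will be adjusted for statistically. The Data analysis section names no covariates.

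One sentence under Experimental and control interventions names a different unit: "Each participant included in the study will be randomized into one of the following two groups".

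**The concern.** Prescribing practice plausibly varies between homes and their visiting physicians, so the effective number of units for balance is 22 homes, not 1,672 residents. A single 1:1 draw of 22 units often leaves some home characteristic uneven.

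The stated remedy is a poor one for two reasons. First, a significance test of a difference between randomized arms asks whether chance produced it, which is already known. It does not ask whether the characteristic predicts the outcome. With 22 homes, a test that respects clustering has little power, so a prognostically important gap can stay unadjusted. Second, the model is settled only after the results have been examined. In an open-label trial with eight listed primary endpoints, that leaves room for data-driven choice.

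At stake are precision that could be had cheaply and the ease of defending the result.

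**Working it through.** **1. Homes per arm.** The abstract gives "A total of 1,672 residents aged ≥ 65 years from 22 nursing homes in South Korea", the recruitment section 76 residents per home, and the sample-size section 836 per group.
- 22 × 76 = 1,672, which matches the stated total.
- 836 / 76 = 11 homes per arm.
- 1,430 / 0.85 = 1,683, against 1,672 stated (0.7% apart).
- 76 × 0.85 = 64.6, about 65 evaluable per home, and 11 × 65 = 715, the stated evaluable number per group.

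The figures fit an 11:11 split.

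**2. Planned effect.** Control rate 40.7% and odds ratio 0.41, both from the sample-size section.
- Odds: 0.407/0.593 × 0.41 = 0.2814.
- Rate: 0.2814/1.2814 = 21.96%.
- Difference: 40.7 − 21.96 = 18.7 points.

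**3. ICC.** The article gives none. Without clustering, 95% power and two-sided 5% need 157 per arm (167 with continuity correction). Then 715/157 = 4.55 and (4.55 − 1)/64 = 0.056; with the correction, (4.28 − 1)/64 = 0.051. I take 0.05 as the working assumption and show 0.03 to 0.10.

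**4. Split of a two-level characteristic.** Suppose 11 of the 22 homes have it (assumption) and 11 are drawn per arm. The probability that k of them fall in one arm is C(11,k)² / C(22,11), with C(22,11) = 705,432.
- 7:4 or worse: 2 × (330² + 165² + 55² + 11² + 1) / 705,432 = 278,544 / 705,432 = 39.5%.
- 8:3 or worse: 2 × (165² + 55² + 11² + 1) / 705,432 = 60,744 / 705,432 = 8.6%.

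Balanced on that characteristic, the split is 6:5.

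**5. Chance gap in baseline PIM users.** SD = √[2 × (ICC + (1 − ICC)/76) × 0.407 × 0.593 / 11], with a normal approximation for the probability.

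| Assumed ICC | SD of gap (points) | P(gap of 5 points or more) |
|---|---|---|
| 0.03 | 4.3 | 25% |
| 0.05 | 5.2 | 34% |
| 0.10 | 7.0 | 48% |

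**6. What a significance trigger would catch.** The article does not say how the test would be done. At ICC 0.05:
- A home-level test (t on 20 degrees of freedom, 2.086) flags only gaps above 2.086 × 5.24 = 10.9 points. Gaps of 5 to 10.9 points would go unadjusted.
- A resident-level test that ignores clustering has SE √(2 × 0.2414/836) = 2.40 points and flags gaps above 1.96 × 2.40 = 4.7 points. That happens in about 37% of draws (4.7/5.24 = 0.90 SD), so whether the covariate enters depends on the draw.

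**7. Possible gain.** Let size and region explain a share R of between-home variance (assumption), with 65 residents per home and ICC 0.05. The SE ratio is √{[0.05(1 − R) + 0.95/65] / [0.05 + 0.95/65]}.
- R = 0.1: √(0.0596/0.0646) = 0.96
- R = 0.3: √(0.0496/0.0646) = 0.88
- R = 0.5: √(0.0396/0.0646) = 0.78

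The SE falls by 4% to 22%.

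**The case against.** The strongest reply is that the article does not say the draw is unrestricted. It is a condensed account, and a fuller protocol may name strata. That stands: silence on strata alone would be no finding. The point survives because the Discussion does state a rule for imbalance, and that rule is weak however the homes were drawn.

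A reader might infer that a plain 1:1 list need not give equal arms, so that 836 per group is not secured. The documents do not support this. Since 836/76 is exactly 11, a fixed 11:11 split is the natural reading, and nothing says each home is allocated by an independent toss.

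A reader might also infer that the trial is biased. It is not, on average. Chance imbalance is part of the sampling variation, and between-home variation appears already allowed for in the roughly 4.5-fold inflation from 157 to 715 per arm.

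The size of the problem should not be overstated. With 11 homes holding a characteristic, 6:5 is the best possible split and 7:4 is the next. If the characteristic moved PIM use by 10 points (assumption), 7:4 would shift the arm difference by 3/11 × 10 = 2.7 points. For one continuous home covariate, a gap above 0.5 SD occurs in 24% of draws and above 1 SD in 2%.

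Finally, no passage shows that size or region predicts PIM use. Size is used only to find replacement homes, and the regions appear only as recruiting associations. This also stands: the precision gain is an assumption.

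**Conclusion.** The point holds in a limited form. As described, the 22 homes are allocated without stated balancing, and the one stated remedy is data-driven and depends on a test with little power at home level. Some imbalance is common (39.5% for a 7:4 split or worse; about one in three for a baseline PIM-user gap of at least 5 points at ICC 0.05). A large imbalance on any one characteristic is uncommon (8.6% for 8:3 or worse). The cost is lost precision and credibility, not bias on average. The ICC, the prevalence of the characteristic and the share of variance explained by size and region are all assumptions.

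The sentence saying each participant is randomized might be read as individual randomization. It is a wording slip: the Aim, Design, Allocation and randomization, and Randomization sections all make the home the unit.

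The change is worth making because it is cheap, and the analysis part remains available even if every home has already been allocated.

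**What to change.** 1. **Discussion, handling of differences between arms.** Replace the significance-triggered rule with covariates named in advance and fitted whatever the observed differences: the resident's T1 value of the outcome, home size and region. This applies in any case.
2. **Allocation and randomization, and Randomization.** For homes not yet allocated, use covariate-constrained allocation on size and region with 11 homes per arm. Separate strata are not advisable: three regions by two size groups is six cells for 22 homes, fewer than four each. Recruitment began in April 2022 and lists were to be drawn beforehand, so allocation may be complete; if so, item 1 alone applies. If a full protocol already sets a restriction, state it here and fit its factors.
3. **Experimental and control interventions.** State that homes are randomized and residents take the arm of their home.

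The cost is a short wait to allocate homes in batches, a revised allocation program and a few degrees of freedom at home level. No extra homes or residents are needed.
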